**1. Summary of the research plan**

**Background:** Unhealthy alcohol use is a leading cause of morbidity and mortality among young adults. Face-to-face brief interventions targeting alcohol use are considered effective in primary care settings, but young individuals tend to have limited contacts with the health care system and are therefore unlikely to receive any intervention. As a result, electronic brief interventions have been developed that can reach a broad population at relatively low cost and potentially impact the public health system. Electronic screening and brief interventions (E-SBI) targeting alcohol use are effective among college students, but more evidence is needed in order to evaluate E-SBI designed for young individuals in other settings. There is also a lack of knowledge about the primary prevention effects of these interventions on, for example, moderate drinkers.

**Specific aims:** We will adapt our website [www.alcooquizz.ch](http://www.alcooquizz.ch) to evaluate the efficacy of a proactive E-SBI providing personalized feedback and information on alcohol use and its consequences among young men in the general population, and to help determine how young men will use E-SBI to obtain information on alcohol use and its consequences.

**Working hypothesis:** It is hypothesized that E-SBI will decrease later alcohol use and related consequences among individuals with unhealthy alcohol use (defined as >=21 drinks/week or at least one episode/month with 6 or more drinks on the same occasion) and will prevent the increase of alcohol use among individuals without unhealthy alcohol use, compared to the control condition. Among individuals with unhealthy alcohol use, the study aims to detect a 3 drinks difference in the mean number of drinks/week at follow-up (1.5 drinks difference among individuals without unhealthy alcohol use) between subjects in the intervention and control groups (alpha level 0.05, 80% power).

**Methods:** Randomized controlled trial: 1080 men will be randomly assigned to receive electronic personalized feedback (n=600) or not (n=600). Participants recruited from the Swiss National Science Foundation supported Cohort study on Substance Use and Risk Factors (C-SURF) will be followed at 1 month and at 6 months. This will be a population-based sample of young French-speaking conscripts from a recruitment center. The primary outcomes will be weekly alcohol consumption and monthly frequency of risky single occasion drinking episodes, defined as 6 or more drinks per occasion. Analyses will be conducted separately for individuals with or without unhealthy alcohol use. The E-SBI will use a website which is structured in French, thus only French-speaking participants from C-SURF will be enrolled in this study.

**Expected value:** From an international perspective, this study will assess E-SBI efficacy in a population-based sample of young men, including potential primary prevention effects among moderate drinkers (who have not been studied extensively). From a national perspective, we know that face-to-face brief interventions conducted in the same setting are effective in decreasing alcohol use, but cannot be offered to everyone due to lack of resources. The proposed research will assess the efficacy of a procedure that could be implemented nationwide and include all conscripts.

KEYWORDS: unhealthy alcohol use, electronic screening and brief intervention, internet, primary and secondary prevention, young adults

# 2. Research plan

**2.1 Current state of research in the field**

***Screening and brief intervention for unhealthy alcohol use***

Unhealthy alcohol use (alcohol consumption that increases the risk of health consequences and includes abuse and dependence) is one of the leading causes of morbidity and mortality among young adults (1, 2). In Switzerland, there is high prevalence of risky single occasion drinking (also called binge drinking), especially among young men (3).

Key issue #1: unhealthy alcohol use is one of the leading causes of morbidity and mortality among young adults

There are major challenges related to unhealthy alcohol use. Most people with unhealthy alcohol use do not seek specialized treatment (4, 5), so efforts have been made to bring services (notably brief interventions) to them. Primary care physicians have been encouraged to provide screening and brief intervention (SBI), which has demonstrated success in reducing alcohol use within primary care settings (6-8), as well as among young individuals (9-11). In spite of the success of SBI delivered in primary care, there are several concerns regarding the feasibility of health care workers finding available resources for teaching and delivering SBI amidst competing priorities and tasks connected to routine medical practices and patient contact (12, 13). In addition, young individuals are unlikely to receive face-to-face SBI because they usually are not sick, and tend to have very limited contact with health care systems.

*Key issue #2: young individuals have limited contact with the health care system, thus are unlikely to receive face to face interventions for unhealthy alcohol use*

***Electronic screening and brief intervention***

As a result, the use of internet and computer-based electronic interventions has been increasing over the past years. It allows the delivery of brief interventions 24 hours a day at the subjects’ convenience in the comfort of their own homes, and gives access to a much broader population than that found in primary care facilities. It is also a relatively inexpensive procedure (14). Most of the known electronic screening and brief interventions (E-SBI) are based on social norms interventions, and contain personalized feedback. According to social norms theory, our perceptions and beliefs of what is “normal” behavior among others will influence our own behavior (15-18). Believing that others drink heavily will impact one’s own drinking. The difference between one’s actual behavior and what one thinks is true of others is considered a “misperception”, and research among college students has established that a high level of misperception is associated with higher levels of alcohol use, and that perceived norms are a strong predictor of alcohol use (18-20). Electronic and face-to-face SBI aiming for the reduction of this misperception (by means of normative feedback) are considered effective for college students (11). In addition to normative feedback, available E-SBIs offer a broad range of personalized feedback and information, such as feedback on blood alcohol concentration (BAC), the monetary impact of alcohol consumption, recommendations regarding drinking, suggestions on how to cut down or on how to avoid risky situations, etc.

[www.alcooquizz.ch](http://Www.alcooquizz.ch), an E-SBI website in French developed in Lausanne, Switzerland, was launched July 15 2010. From July 15 to August 15 2010, 13,427 individuals accessed the website, of whom 11,472 (85%) fully completed the assessment and received personalized feedback. The mean age (SD) was 36.6 (13.0), 68.6% were men, and 57.7% had an Alcohol Use Disorders Identification Test >8 (21, 22), indicating probable problem drinking. Men reported a mean of 15.3 drinks per week and women a mean of 9.0 drinks per week. E-SBI appears to be feasible in Switzerland, since more than half of those accessing the website had AUDIT scores >8.

Most of the published literature on E-SBI targeting alcohol use are results from North-America (USA and Canada) and Australia or New Zealand studies, conducted primarily among college student populations (23-28). Several studies have been conducted in the UK and Finland (29, 30). Other studies conducted in the general population indicate that E-SBI is also a valuable strategy within non-student populations (14, 31, 32). However, as reported in a 2009 Cochrane review (11), more evidence of efficacy for young individuals other than college students is needed.

Key issue #3: an electronic brief intervention is an opportunity to reach a wide population, but more evidence is needed on its efficacy among young individuals outside of college settings

Most published studies have focused on individuals with unhealthy alcohol use. E-SBIs, when made available for the general population, are likely to be used also by individuals with moderate drinking or abstinence. It is therefore important to know what impact these intervention can have on moderate drinkers or abstainers. Providing information on alcohol use and its consequences may help prevent possible increases in use among low-risk drinkers. Nevertheless, there is a lack of knowledge about the primary preventive effects of E-SBI. The use of E-SBI for primary prevention (i.e. future unhealthy alcohol use among individuals with moderate drinking or abstinence) and secondary prevention (i.e. decreasing alcohol use among individuals with unhealthy alcohol use, before the development of life threatening medical consequences) among a population-based sample of young men will give important information regarding its efficacy and feasibility. Young men are the most likely to benefit from reduction in alcohol use since they account for a high proportion of unhealthy alcohol users, with high rates of risky single occasion drinking (33).

**The proposed project will test the efficacy of an E-SBI for unhealthy alcohol use in a population sample of Swiss young men, using a primary and a secondary prevention approach.**

**2.2 Detailed research plan**

**2.2.1 Aims**

We propose to test the hypothesis that E-SBI targeting alcohol use delivered by the internet will improve drinking outcomes among young men. It is hypothesized that E-SBI will decrease later alcohol use and related consequences among individuals with unhealthy alcohol use and prevent any increase in alcohol use among individuals who do not engage in unhealthy use. In addition, since the proposed intervention offers access to many resources, such as information and fact sheets, we can determine the access and usage rates among young adults.

**2.2.2 Rationale**

Switzerland has a mandatory army recruitment process, thus presenting a unique opportunity to access the entire population at a given age. The impact of E-SBI in the general population can be evaluated, within a setting conducive to later implementations of the inventions. The proposed project will take advantage of an ongoing study supported by the Swiss National Science Foundation (SNF grant 33CSCO-122679): the Cohort study on Substance Use and Risk Factors (C-SURF) and recruit participants for the proposed project from among the subjects there. The E-SBI study will be a large nested project integrated with C-SURF.

French-speaking young men are currently recruited within the Lausanne army recruitment center. Since the recruitment procedure is mandatory (and C-SURF has no *a priori* exclusion criterion), virtually all French-speaking Swiss 19-year-old men are eligible for enrollment. In collaboration with the C-SURF team, participation in the present project will be offered to all French-speaking cohorts. This will allow E-SBI to be studied within a well-characterized population of young men drawn from the Swiss general population.

From a public health point of view, the young men in this population are of great interest since they frequently drink amounts of alcohol that put them at risk for damaging consequences (2, 3, 33). Preventing or decreasing unhealthy alcohol use in this population will have important public health implications. As stated earlier, since this population is mostly healthy and consequently do not usually access the health care system, new ways of delivering personalized interventions need to be developed. E-SBI represents a potentially effective option, since young men frequent the internet often. Therefore, this population is of particular interest for researching E-SBI.

From a national perspective, face-to-face brief interventions conducted at the recruitment center in Lausanne have proven to be effective in this population, showing a 20% reduction in weekly alcohol consumption six months after baseline (34). Because resources are not available for delivering face-to-face intervention to everyone attending recruitment centers, electronic alternatives represent an opportunity to extend this service to a wider base of potential recipients**.**

***Strengths:***

The Alcohol treatment center research group ([name], [name], [name], [name] and [name]) has been conducting studies at the army recruitment center in Lausanne since 2006 and has developed a strong research history within this setting, including a large randomized controlled trial of face-to-face brief intervention. The C-SURF project takes place in this setting. More so than other studies in the field, C-SURF collects extensive data; this furnishes detailed descriptions of all E-SBI participants. C-SURF procedures (e.g. the tracking team and up-to-date address registry) should help ensure low drop-out rates for the proposed project. Later on, if short or medium term effects of E-SBI are shown, the C-SURF follow-up will allow the evaluation of long term effects of E-SBI.

The Clinical Research Center (CRC) of the CHUV will be involved in the management and analysis of the data. This collaboration will help maintain a high level of methodological quality in the E-SBI component.

**2.2.3 Methods**

***Study design***

This will be a randomized, controlled clinical trial evaluating the impact of E-SBI on alcohol use. All participants who meet the eligibility criteria will be randomized into either of these groups; intervention or control. Screening and/or baseline evaluation will be done, with follow-ups at one month and at 6 months after randomization. The first follow-up will allow assessment of the relatively short-term result from the intervention. The one-month and the 6-month assessments will be done electronically. The study design is presented in Figure 1

# Figure 1: Study design

*Census of young French-speaking men*

*C-SURF participants (n=3500)*

Individuals invited to participate (n=3500)

No access to the website

or decline participation

Individuals completing the baseline assessment (n=1200)

Random allocation* (n=1200)

Control (n=600)

Intervention (n=600)

1 Month Electronic follow-up assessments

(n=960)

6 Month Electronic follow-up assessments

(n=900)

Alcohol consumption

* Participants will fill out the baseline assessment and then be immediately randomized. Participants assigned to the intervention group will receive the intervention at this time

# *Definition of the study population*

The study population will consist of 20-year-old, French-speaking Swiss men participating in the C-SURF cohort project. As stated before, C-SURF has no *a priori* exclusion criterion, so virtually all men showing up for the mandatory recruitment procedure will be eligible. The recruitment facility at Lausanne is the only center in the French-speaking sector of Switzerland, allowing a broad spectrum of young men (not limited to college students) to be reached. Since we propose adapting the website that currently is entirely in French, we will limit our inclusion to C-SURF participants who speak French (n=3500).

## *Inclusion criteria for the proposed project (no hierarchical order)*

1. Participants must be part of C-SURF
2. Participants must read French and provide informed consent.
3. Participants must be willing to be randomly assigned to an intervention or a control condition and agree to complete follow-up assessments.

## *Exclusion criteria (no hierarchical order)*

No specific exclusion criterion has been retained for the present study.

## *Efficacy measures*

### *Primary outcomes*

1. Weekly alcohol consumption (number of drinks per week, where one drink contains 10g of ethanol)
2. Monthly frequency of Risky Single Occasion Drinking episodes (RSOD corresponding to 6 or more drinks per occasion)

### *Secondary outcomes*

### Number of consequences due to alcohol (was injured or injured someone else, had a hangover, missed a class or work, performed poorly at work, did something that was later regretted, had a blackout, got into an argument or fight with friends, had unplanned sex, had unprotected sex, damaged property, had problems with the police, received medical treatment, observed negative impact on physical health, and observed negative impact on mental health)

### Computed Blood Alcohol Concentration (BAC), based on maximum reported alcohol consumption since previous assessment

### Presence of unhealthy alcohol use (>=21 drinks per week or at least one RSOD episode per month)

### Use of the website

***Study intervention***

The electronic intervention includes self-assessment of current alcohol use and consequences, personalized feedback on alcohol use, and general information on alcohol use and its consequences (i.e. “fact sheets”). E-SBI personalized feedback will be adapted from [www.alcooquizz.ch](http://www.alcooquizz.ch) and will consist of:

- Normative feedback (comparison of the participant’s alcohol consumption per week and per occasion to the consumption of individuals of the same age in the Swiss population, based on data from the Swiss Health Survey (35) with more than 12,000 participants).
- Feedback on reported consequences
- Calorific value of reported consumption
- Computed BAC based on maximum reported alcohol consumption, and potential consequences
- Indication of risk category (i.e. presence or absence of episodic risky drinking and/or weekly risky drinking, and probability of alcohol-related problems)

Participants who report unhealthy alcohol use will be encouraged to modify their drinking habits, and be presented with the rationale for risks associated with their current use of alcohol. They will be asked whether or not they intend to change their drinking habits, in order to enhance thoughts about change and to characterize participants in terms of motivation to change. According to motivational interviewing theory, encouraging people to envision hypothetical change helps them take steps towards that change (36). Participants will have the opportunity to print their personalized feedback form, and will be able to access a section containing general information on alcohol use and its consequences.

##

## *Control group*

Participants randomized into the control group will complete the same baseline assessment as do members of the intervention group, but will neither receive personalized feedback nor have access to the general information section on the website.

## *Time to complete the assessment*

The approximate time to complete the baseline assessment is three minutes. All participants will be asked if they think that the internet is a suitable option for providing personalized information about substance use.

### *Recruitment*

After giving informed consent to participate in C-SURF, subjects are told that they are likely to be offered participation in another study. Invitations will be sent via e-mail to C-SURF participants (most C-SURF procedures are already electronic) that contain a description of the E-SBI study and a unique identifier. Invitees will be instructed to go to the study website, enter their unique identifier and complete the on-line assessment if they agree to participate, or to indicate that they decline. In case of non-response, a maximum of two reminders will be sent. The website log linking subject addresses to their unique identifiers will be kept separate in order to preserve confidentiality.

### *Randomization*

Randomization will be processed (unseen) in the website background, using an automated randomization procedure that has been used in other studies in the field. Following the assessment, the web server software will randomly assign participants to either receive the intervention or not. This selection will be based on the order in which participants accessed the website and stratified by drinking status (unhealthy alcohol use yes vs no). None of the study personnel will be involved in the process, thus all allocations will be anonymous.

***Technical support***

A research associate will be hired to manage the transfers between the C-SURF database and the website coordinators, to contact non-responders, and to oversee and coordinate recruitment for the E-SBI study according to the C-SURF calendars and schedules. Study personnel will be available during business hours (and afterwards by e-mail) to answer all questions about using the website.

***Follow-up period***

Participants will be contacted by e-mail one week prior to each follow-up point. They will receive a unique identifier and will be asked to log on to the website and complete the follow-up assessment within one week. Those who do not complete the assessment will receive up to three e-mail reminders, followed by three additional reminders via telephone. This same procedure will be used at the 6-month follow-up. All follow-up assessments will be scheduled according to the initial date of randomization, which is considered Study Day 1.

###

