**2.3.4 Data and data collection**

### *Instrument to evaluate the outcome*

The assessment at baseline and at each of the two follow-up points will consist of a self-completed electronic questionnaire that will include validated instruments and additional questions. Alcohol consumption will be collected via quantity/frequency questions (“In a given day that you use alcohol, how many drinks are you drinking?” / “On how many days in a regular week are you drinking alcohol?”). Additionally, participants will complete the Alcohol Use Disorders Identification Test (AUDIT)(21, 22). The AUDIT is a 10-question measure that has been extensively studied and validated, and has been used successfully in other electronic brief interventions (14, 27). Participants will also report their heaviest alcohol use on a single occasion over the past 3 months. Alcohol-related consequences will be assessed using 12 questions adapted from a questionnaire developed by Wechsler et al., 1994 (37). Subjects will be asked two supplemental questions about the impact of alcohol on their physical and mental health (“Over the past year, do you think your alcohol drinking had a negative impact on your physical health” / “your mental health?”).

Identical measures will be used at baseline and at each of the two follow-ups. When necessary, questions that are time-referenced (e.g. “over the past x months…”) will be adapted to accommodate each of the follow-up points (i.e. “over the past month…”, “over the past 5 months…”, or “since the last time we asked you about your drinking...”).

Statistics on website use (e.g. number of topics accessed, time spent on the feedback, etc.) will be collected for each participant.

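### Opening the 1-month questionnaire a week early lets any item with past-month recall reach up to 7 days before randomisation

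*Protocol*

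**What the plan says.** **Timing (Protocol 2.2.3, Follow-up period).** "Participants will be contacted by e-mail one week prior to each follow-up point". With that e-mail participants receive their identifier and "will be asked to log on to the website and complete the follow-up assessment within one week". Non-responders are then pursued: "Those who do not complete the assessment will receive up to three e-mail reminders, followed by three additional reminders via telephone". The clock is explicit: "All follow-up assessments will be scheduled according to the initial date of randomization, which is considered Study Day 1". No earliest completion day and no closing date are given.

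**Recall (Protocol 2.3.4, Instrument to evaluate the outcome).** The same measures are used at all three assessments. Where necessary, questions that carry a time reference "will be adapted to accommodate each of the follow-up points". Three example wordings follow: one for the past month, one for the past five months, and one that counts from the last time the participant was asked. They are not assigned to particular items. Weekly consumption comes from a quantity question and a frequency question, the latter reading "On how many days in a regular week are you drinking alcohol". Neither has a dated window. No recall period is given there for the RSOD item.

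**Use of the data.** Under Study design, "The first follow-up will allow assessment of the relatively short-term result from the intervention". The Efficacy analysis section bases the efficacy analyses on the baseline, 1-month and 6-month data.

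**The concern.** The two sections do not fit together. If the 1-month questionnaire is answered on time, less than a full month has usually passed since randomisation. A question about the past month then reaches back into days before the participant had been allocated to anything.

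On those days the arms cannot differ because of the intervention. Counting them as follow-up mixes a period of zero effect into the outcome and shrinks the expected difference. The amount depends on when the man answers: most for those who respond on the day of the e-mail, none for those who respond after reminders. The same item would thus measure different things in early and late responders.

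The primary outcomes are weekly consumption and monthly RSOD frequency, and neither has a recall window tied to randomisation. By contrast, the secondary blood alcohol outcome is defined from the maximum intake since the preceding assessment. Recall cannot be repaired after the data are collected.

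**Working it through.** **Inputs**
- E-mail sent 7 days before the follow-up point; completion asked for within 7 days (Follow-up period).
- Time origin: randomisation (same section).
- Candidate recall windows: past month, past five months, or since the previous questionnaire (Instrument to evaluate the outcome).
- Assumptions: a month is 28, 30 or 31 days; six months is about 183 days and five months about 152. The protocol gives no distribution of response days, so only the range can be shown.

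The protocol states no figure for this overlap, so there is none to reproduce.

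**Step 1: when on-time answers arrive.** With a 30-day month, the range runs from 30 − 7 = day 23 to day 30.

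**Step 2: share of a past-month window that precedes randomisation.** Share = days answered early ÷ length of the month.

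| Answered | 28-day month | 30-day month | 31-day month |
|---|---|---|---|
| 7 days early | 7/28 = 25.0% | 7/30 = 23.3% | 7/31 = 22.6% |
| 3.5 days early | 3.5/28 = 12.5% | 3.5/30 = 11.7% | 3.5/31 = 11.3% |
| At or after one month | 0% | 0% | 0% |

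**Step 3: what this does to a difference.** Suppose the effect is nil before randomisation and constant afterwards, and the item averages evenly over its window. Then the expected recorded difference = true difference × (1 − share). With a 30-day month that is 1 − 0.233 = 0.767 of the true difference for an answer on the day of the e-mail, and 1 − 0.117 = 0.883 at mid-window. These factors apply to past-month items only. If the RSOD item is one of them, they apply to it, but the protocol gives no planned RSOD difference to which they could be applied.

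**Step 4: the alternative wording.** Counting from the previous questionnaire starts the window at baseline, so the overlap is zero on any response day. The window is then about 23 days for the earliest responder, 30 for one answering on the due date, and longer after reminders. A raw count over 23 days covers 23/30 = 77% of a month, so a monthly frequency would need rescaling, which the protocol does not mention.

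**Step 5: the weekly-drinks items.** They have no dated window, so there is no denominator and no share can be computed.

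**Step 6: six months.** The earliest on-time answer is at 183 − 7 = day 176. Five months of recall starts at 176 − 152 = day 24 after randomisation. There is no overlap.

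**The case against.** The case against has several sound parts.

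- **The overlap is conditional.** The sentence that lists past-month recall also lists the wording that counts from the previous questionnaire. A reader might infer that the 1-month outcome does include drinking before randomisation. The text does not establish that; it permits it.
- **The planned effect cannot be discounted.** It is tempting to take the 3.0 drinks/week used in the sample size, multiply by 23/30 and report 2.30. The protocol does not support this. The 3.0 refers to weekly drinks, whose questions are undated, and a past-month share cannot be applied to them. Nor does an undated present-tense question show that earlier drinking is counted: it may be read as asking about the habit at the time of answering. What can be said is that its reference period is undefined.
- **The upper figure is an extreme.** It needs past-month wording, an answer on the day of the e-mail and exact recall by day. The reminders imply that some men will answer after a full month, with no overlap.
- **The direction is conservative.** The procedure is the same in both arms, so the expected result is dilution and not a spurious benefit.
- **The 6-month comparison is untouched**, and the sample size allowance for attrition refers to that visit.

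These points limit the size and reach of the concern but do not remove it. The early opening is a stated rule, the past-month wording is a stated option, and the protocol uses the 1-month data for efficacy. A questionnaire specification not at hand might assign wordings to items. Even so, the early window would leave either overlap (past month) or windows of unequal length (since the last questionnaire).

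**Conclusion.** The concern holds in a limited form. The timing rule and the recall options, taken together, allow an on-time 1-month answer to a past-month item to include up to 7 days before randomisation. That is at most 23-25% of the window, about 12% at mid-window, and zero from one full month onward. Any such item would show a 1-month difference biased towards zero, to a degree that varies with response day.

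This rests on four assumptions: past-month wording is actually used, recall is spread evenly over the window, the intervention has no effect before randomisation, and response days are distributed similarly in the two arms. The average dilution across participants cannot be stated, because the distribution of response days is unknown.

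For the weekly-drinks outcome the conclusion is only that the reference period is undefined. No loss of effect or power can be attached to it. The 6-month assessment is not affected. The change is worth making before launch because it is cheap and the defect cannot be corrected afterwards.

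**What to change.** 1. In the Follow-up period section, separate the notice from the opening of the questionnaire. An advance e-mail may still go out a week ahead, but the 1-month questionnaire should open no earlier than one full month after randomisation.
2. Reconcile that section with the instrument section by stating, item by item, the recall wording at 1 month. For the RSOD item and the quantity/frequency items, the window should start at or after randomisation.
3. If the wording that counts from the previous questionnaire is chosen for a frequency item, state how the count is converted to a monthly rate.

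No change is needed at 6 months on grounds of overlap.

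**Cost:** a date setting on the website and a wording revision before launch. The 1-month data arrive up to one week later.
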